**Fig. 4 Fig4:**
[figure not shown]
**a** Sagittal contour of the distal femur. The sagittal profile lines are oriented with between the intersection of the posterior condylar offset (PCOi) and the outer border of the native bone or femoral component (shown here). For the profile, five lines are plotted: straight anterior (ANT), anterior at 30° (ANT30), straight distal (DIST), posterior at 30° (POST30), and straight posterior (POST). **b** The orientation of the 3 sagittal slices of the femur where the sagittal profile is calculated: (1) the medial slice, (2) the trochlea slice, and (3) the lateral slice. All slices are oriented perpendicular to the line through the PCOi (see **a**)

### Primary study parameter

The flexion angle of the TKA in the sagittal plane is measured to determine difference in femoral component placement between the groups. This angle is commonly defined as the angle ‘*γ*’ between the bone stub axis (BSA) of the femur [25] and the neutral line of the femoral component of the prosthesis [12] (Fig. 3). Due to artifacts in the fluoroscopic assessment caused by the metal in the prosthesis, the neutral line is unidentifiable. However, the most anterior plane on the inside of the femoral component of the prosthesis, the frontal flange, can be detected in the fluoroscopic assessment (Fig. 3). Therefore, the angle ‘*θ*’ between the frontal flange and the BSA is measured. The angle between the frontal flange and the neutral line is 97°; thus, the formula *γ* = *θ* − 7° can be used for future comparison between gamma and theta measurements. To obtain the angle ‘*θ*’, the BSA is aligned with the vertical *y*-axis by coronal and sagittal rotating the 3D volume image. Furthermore, the transversal plane is rotated towards an anatomic orientation to correct any femur rotation deviations from acquisition. The latter is necessary to be able to compare different cases. Once the orientation of the femur is standardized within the 3D volume image, the frontal flange can be manually annotated and compared with the *y*-axis, the BSA. For annotation, the sagittal slice with the most prominent frontal flange is chosen and to minimize measurement error from manual annotation an average over 5 iterations is used. We hypothesize that the flexion angle will be larger in the flex rod group (i.e., better fit to the distal anatomy of the femur, Fig. 2).

### Secondary study parameters

The sagittal profile is calculated as the length of lines connecting the intersection of the posterior condylar offset of the distal femur in the sagittal plane (PCOi), and the outer border of either the native femur or femoral component (Fig 4a). The PCOi must be at the exact same location before and after TKA to allow comparison. For this reason, the 3D volume images from before and after TKA are aligned using an automatic intensity-based images registration algorithm in Matlab, based on the shaft of the femur. For constant measurements, the exact same slice has to be selected in every subject. To achieve these constant measurements we pre-align a random 3D volume image with a prosthesis as calibration set. The 3D volume images after TKA are aligned with this calibration set using the same intensity-based image registration algorithm. Subsequently, the pre-operative images (without TKA) are aligned using the same transformation variables.

Due to artifacts in the 3D volume images, the sagittal profile of the trochlea is unidentifiable and sagittal profiles of the condyles are affected. For the best representation of the sagittal profiles, the original designs of the manufacturer are converted into a 3D volume image and added with the pre-aligned calibration set. To avoid image registration errors a pre-aligned calibration set is created for each prosthesis size.

The sagittal profiles of the native femur and the TKA will be calculated at 3 slices: (Fig. 4b) (1) the slice through the most distal point on the medial condyle, oriented at 17.1% of the prosthesis width from the medial side; (2) the slice through the trochlea at the most cranial point of the distal femur, oriented at exactly the middle of the prosthesis; and (3) the slice through the most distal point on the lateral condyle, oriented at 17.1% of the prosthesis width from the lateral side.

One goal of the TKA procedure is restoration of the joint line. This would mean that the amount of implant material at the medial and lateral condyle in full extension of the knee is ± 1 mm from the native situation (DIST, Fig. 4b). A second goal is restoration of the flexion radius. This is operationalized as the amount of implant material at straight posterior at 90° of knee flexion (POST, Fig. 4b) which should be the same as in the native situation (± 1 mm). For mid flexion stability (at 30° of knee flexion), it is also important that the amount of implant material equals the native situation (FLEX30, Fig. 4b). Patellofemoral function can be determined at the trochlear slice. At PCO straight anterior (ANT, Fig. 4b), the amount of implant should equal the amount of native bone (± 1 mm). When the knee flexes, the patella rests on the medial and lateral condyles instead of in the trochlea. So also on the medial and lateral slices at 30° from straight anterior, the length will be calculated (ANT30, Fig 4b). The lengths of the sagittal profile lines are automatically calculated based on pixel density as representative for bone density. In case the segmentation of the femur is incorrect due to artifacts (caused by other bone density than the algorithm expects due to osteoporosis, sclerosis, lower radiation dose, etc.), the lengths are manually corrected. For all five lines, the length in the native situation is subtracted from the length in the component, resulting in a positive sign when the implant is bigger than the native femur (i.e., “overstuffing”), and a negative sign when the implant is smaller than the native femur (i.e., “understuffing”). The margins are defined as ± 1 mm (range of 2 mm). We hypothesize that the differences of the anterior and posterior sagittal contours on the three slices between the pre-operative situation and the post-operative image will be smaller in the flex rod group (i.e., better fit). In the images of the native femur, articular cartilage cannot be seen [20]. Therefore, an average cartilage thickness of 2 mm will be added to the lengths in the native femur [20].

### Functional outcome

Functional outcome will be measured using (1) the timed Get-up and Go test, to measure functional mobility [27]; (2) the stair climbing test to measure ability to ascend and descend a flight of stairs of 14 steps [28]; (3) the Leg Extensor Power Rig (Queens Medical Centre, Nottingham, UK) to measure knee power output [4, 15]. The rig consists of a seat and footplate connected via a lever and chain to a flywheel. Application of force accelerates the flywheel from rest and output is recorded as both maximal wattage (W) generated and as relative power-bodyweight ratio (%) of a single leg extension. The power output is recorded five times per leg and the highest output of the leg in study will be used for analysis and (4) Oxford Knee Score [10], KOOS-PS [26], KUJALA patella score [22], and Knee Society Score [19] to measure patient and clinician reported outcomes. Table 2 shows the schedule for the functional outcome measurements. The hypothesis is that patients in the flex rod group will have better results on all functional outcome scores.

**Table 2 Tab2:** The surgical study parameters

Parameter	Scale or units	Scored by	Details
Sagittal thickness of the bone cuts during surgery	mm	Surgeon	The bone cuts are posterior cut of patella, anterior cut medial condyle, anterior cut trochlea, anterior cut lateral condyle, anterior 45° cut medial condyle, anterior 45° cut trochlea, anterior 45° cut lateral condyle, distal cut of medial condyle, distal cut of lateral condyle, posterior cut of medial condyle, and posterior cut of lateral condyle. Measured using a Vernier caliper.
Cartilage score of the bone cuts	No, partial, good	Surgeon	See above for the bone cuts
Area of bone cuts	mm^2^	Researcher	All bone cuts are placed with the cut side facing a standardized reference sheet, photographed, and post-operative the area is measured using ImageJ
Cut bone not covered by implant, in mediolateral direction by medial and lateral coverage with implant	mm	Surgeon	Measured per-operative by the surgeon using a Venier caliper. This distance will be measured at the intersection of the anterior chamfer cut and the neutral of the component, at the ventral part of the indention on the component and at the intersection of the neutral of the component and the dorsal chamfer cut
TKA procedure time	min	n/a	Collected post-operatively from hospital information system
Recut or sizing problem	n/a	Surgeon	
Number of releases of collateral ligaments	n/a	Surgeon	
Size of components	n/a	n/a	Collected post-operatively from hospital information system
Intra-operative complications	n/a	Surgeon	
Tourniquet time	min	n/a	Collected post-operatively from hospital information system

### Other study parameters

#### Baseline information

The following demographic and disease-related data will be collected pre-operatively: age, gender, height, weight, strength (Medical Research Council scale), physical activities (UCLA activity score [2]), primary diagnosis, side, alignment of involved knee, and previous surgery of the affected knee.

#### Operative information

See Table 2 for an overview of the parameters recorded during surgery.

#### Radiological information

The following radiological parameters will be measured (see Table 3 for an overview of the radiology schedule): (1) posterior condylar offset (PCO) measured on regular true lateral X-ray [5], (2) patellar tendon angle (PTA) measured on weight bearing with 45° flexion lateral X-ray; (3) lateral patellar tilt [23], and lateral patellar displacement of patellofemoral joint measured on supine sky-line patella X-ray [14], (4) Slope of the tibial component with respect to the tibia measured on the post-operative lateral X-ray.

**Table 3 Tab3:** Schedule of functional outcome and radiological measurements

Parameter	Visit			
	Pre-operative	3 months	12 months	24 months
Fit (flexion angle and sagittal profile)	Multi Diagnost Eleva, supine	Multi Diagnost Eleva, supine	-	-
Functional outcome	Time Get-up and Go test, stair climbing test, Leg Extensor Power Rig	Time Get-up and Go test, stair climbing test, Leg Extensor Power Rig	Time Get-up and Go test, stair climbing test, Leg Extensor Power Rig	Time Get-up and Go test, stair climbing test, Leg Extensor Power Rig
Posterior condylar offset	Lateral x-ray, standing	Lateral x-ray, standing	Lateral x-ray, standing	-
Patellar tendon angle	Lateral x-ray, standing, 45° flexion	Lateral x-ray, standing, 45° flexion	Lateral x-ray, standing, 45° flexion	-
Patellar tilt and displacement	Sky-line patella x-ray, supine	Sky-line patella x-ray, supine	Sky-line patella x-ray, supine	-

All patients will receive post-operative standard care according to the usual practice of our hospital. Post-operative blood loss and/or complications will be documented on the case report form. Post-operative data through time of hospital discharge will be reported on the discharge form.

#### Statistical analysis

Sagittal flexion angle of the TKA will be reported as mean and standard deviation (or median and interquartile range (IQR)). An independent two-sample *t* test (or non-parametric equivalent) will be used to analyze the effect of group (flex rod versus standard rod). All secondary outcome parameters will be reported as mean and SD (or median and IQR). Repeated mixed model analysis techniques will be used to analyze the effects of group, time, and their interaction. All other study parameters will be reported as mean and standard deviation (or median and IQR). Independent *t* tests (or non-parametric equivalent) and Chi square (in case of frequencies) will be used to analyze the effect of group. All statistical analyses will be performed using Stata/IC for Windows, Release 13 (StataCorp LLC, College Station, TX, USA).

The sample size calculation is based on the primary study parameter: flexion angle of the prosthesis in the sagittal plane. Our hypothesis is that this angle at 3 months will be smaller in the standard rod group compared to the flex rod group. First, the flexion angle in posterior stabilized TKA has been reported to be about 6° [1]. Second, the mean intra-observer difference between measurements for this angle is 2.3° with an estimated standard deviation of 5° [16]. We assume that a clinical relevance of a mean difference of 5° between the rod groups can be measured [21], but this will be further studied in our study. Using G*Power (version 3.1.7 [11]), a sample size was calculated for an independent two-sample *t* test, with the variables *m*1 = 6°, *m*2 = 11°, *σ*1 = 5°, *σ*2 = 5°, *α* = 0.05, and power = 0.80. This calculation yielded a sample size for the total group of *N* = 54, with 27 for each group. Taking into account a drop out of participants during the course of the study of 10%, a sample size of *N* = 60 subjects is needed, with 30 subjects in each group.

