### Design and setting

A single-blind randomized controlled trial with two groups (flex rod vs standard rod), with the participants blinded for group allocation. Participants will be measured on five occasions in our outpatient clinic (pre-operative, per-operative/post-operative, 3 months, 1 year, and 2 years post-operative). The study ends after 2- year follow-up. The trial has been set up according to CONSORT guidelines [29], and ethical approval for this study was obtained from *Medisch-ethische toetsingscommissie Slotervaartziekenhuis en Reade* (approval ID P1453).

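### The stated analyses name no baseline adjustment for the repeated X-ray and functional outcomes, which costs precision; the X-ray t tests are unbiased

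*Protocol article*

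**What the plan says.** All references are to the protocol article.

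- **Secondary outcomes** (Statistical analysis): "Repeated mixed model analysis techniques will be used to analyze the effects of group, time, and their interaction". By the order of the headings this covers the functional outcomes. The text does not say which visits are responses, what role the pre-operative value has, or which term carries the rod effect.
- **Other study parameters** (Statistical analysis): "Independent *t* tests (or non-parametric equivalent) and Chi square (in case of frequencies) will be used to analyze the effect of group". The Radiological information section stands under the Other study parameters heading, so its X-ray measures fall under this sentence.
- **Schedule** (Design and setting; Table 3): "Participants will be measured on five occasions in our outpatient clinic (pre-operative, per-operative/post-operative, 3 months, 1 year, and 2 years post-operative". Table 3 lists the functional tests, "Time Get-up and Go test, stair climbing test, Leg Extensor Power Rig", at the pre-operative, 3-, 12- and 24-month visits. It lists posterior condylar offset, patellar tendon angle, and patellar tilt and displacement pre-operatively and at 3 and 12 months.
- **Sagittal profile** (Secondary study parameters): "For all five lines, the length in the native situation is subtracted from the length in the component". It is therefore already a post-minus-pre difference, and Table 3 gives it one post-operative scan.
- **Primary outcome** (Statistical analysis): "An independent two-sample *t* test (or non-parametric equivalent) will be used to analyze the effect of group (flex rod versus standard rod". A component angle has no pre-operative counterpart.

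**The concern.** Randomisation makes the expected group difference zero before surgery, and the hypotheses concern what happens afterwards. A pre-operative value is therefore most useful for removing between-patient variation from the post-operative comparison. The stated methods do not use it that way.

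For the three groups of X-ray measures, a two-group t test at a follow-up visit discards a value that has already been collected. For the functional tests, the listed terms leave two plain readings. If the pre-operative visit is left out of the model, the baseline is not used at all. If it is one of the time levels, the group main effect averages in a visit with no expected difference, and the interaction uses the baseline only as a change score.

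The stake is precision. The trial was sized on the flexion angle alone, while the Functional outcome section hypothesises an advantage for the flex rod on every functional score. About 27 evaluable patients per arm leave little precision to give away on those outcomes.

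**Working it through.** **The plan's own figure.** The article gives no power, SD or target difference for the functional or X-ray outcomes, so there is nothing to reproduce on this point. From its sample-size paragraph I take only the 27 evaluable patients per arm (54 in total; 54/0.9 = 60 enrolled).

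**Assumptions not in the documents.** Unit SD at each visit; the same correlation ρ between any two visits, set at 0.3, 0.5 and 0.7; a constant effect of 0.6 SD at every post-operative visit; complete data; two-sided α = 0.05; normal approximation.

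**General formula.** SE = √(2V/27) and power = Φ(estimate/SE − 1.96), where V is the per-patient variance of the contrast.

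**1. X-ray outcomes at one follow-up visit**

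- t test on the post-operative value: V = 1. It estimates the full effect.
- Baseline-adjusted: V = 1 − ρ². It also estimates the full effect.

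| ρ | V adjusted | Patients the t test needs, relative to adjusted, 1/(1−ρ²) | Power, t test | Power, adjusted |
|---|---|---|---|---|
| 0.3 | 0.91 | 1.10 | 0.60 | 0.64 |
| 0.5 | 0.75 | 1.33 | 0.60 | 0.72 |
| 0.7 | 0.51 | 1.96 | 0.60 | 0.87 |

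For example, at ρ = 0.5 the t test has SE = √(2/27) = 0.272 and 0.6/0.272 = 2.20. The adjusted analysis has SE = √(1.5/27) = 0.236 and 0.6/0.236 = 2.55.

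**2. Functional tests, one pre-operative and three post-operative visits**

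- Group main effect over all four visits: estimate (0 + 3 × 0.6)/4 = 0.45, which is 0.75 of 0.6; V = (1 + 3ρ)/4.
- Group-by-time contrast (mean post-operative value minus pre-operative value): estimate 0.6; V = (4/3)(1 − ρ).
- Post-operative mean without baseline: estimate 0.6; V = (1 + 2ρ)/3.
- Baseline-adjusted post-operative mean: estimate 0.6; V = (1 + 2ρ)/3 − ρ².

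| Contrast | V at ρ = 0.3 / 0.5 / 0.7 | Power at ρ = 0.3 / 0.5 / 0.7 |
|---|---|---|
| Group main effect, four visits | 0.475 / 0.625 / 0.775 | 0.67 / 0.55 / 0.47 |
| Group-by-time contrast (1 df) | 0.933 / 0.667 / 0.400 | 0.63 / 0.77 / 0.94 |
| Post-operative mean, no baseline | 0.533 / 0.667 / 0.800 | 0.86 / 0.77 / 0.69 |
| Baseline-adjusted post-operative mean | 0.443 / 0.417 / 0.310 | 0.91 / 0.93 / 0.98 |

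For example, at ρ = 0.5 the group-by-time contrast has SE = √(2 × 0.667/27) = 0.222 and 0.6/0.222 = 2.70. The adjusted mean has SE = √(2 × 0.417/27) = 0.176 and 0.6/0.176 = 3.41.

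An overall 3-df test of the same interaction has power 0.61 at ρ = 0.5 and 0.85 at ρ = 0.7. The article does not say that this test would be the one used.

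The fair comparison for a sensible reading of the mixed model is therefore the 1-df contrast. Adjustment gains about 16 points at ρ = 0.5 and 4 points at ρ = 0.7.

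**The case against.** A reader might infer that the model treats the pre-operative visit as an outcome visit and so dilutes the rod effect, and that the X-ray t tests dilute it too. The documents do not support this.

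- The Statistical analysis section never says that the pre-operative visit is a response. Table 3 is a measurement schedule and specifies no model. The remedy itself contains group, visit and their interaction, so the quoted sentence is compatible with it. A condensed article may leave the baseline's role and the deciding contrast to a fuller document.
- The factor 0.75 applies only if the pre-operative visit is a time level and the group main effect is read as the rod effect. The article also names the interaction, which estimates the effect in full.
- In a randomised trial a post-operative t test is unbiased. It is only less precise.
- It would also be too strong to say that the mixed model wastes the baseline, because the group-by-time contrast uses it as change.
- The correlations are unknown. The X-ray measures compare a native with an implanted knee, so ρ may be low; at 0.3 the variance saving is 9%. The text also does not say whether these measures are tested as raw values or as change.

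All of this stands, and it limits the point to precision. It does not remove the point. The article does state a test for the X-ray measures and a list of terms for the mixed model, and neither names a baseline covariate or constraint. Of the full-effect contrasts computed, the baseline-adjusted one has the highest power at each correlation tried.

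**Conclusion.** The point holds as one of efficiency. It does not show bias.

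It is firmest for posterior condylar offset, patellar tendon angle, and patellar tilt and displacement, because the analysis sentence and Table 3 establish it without any inference about a model. The price of the plain t test depends on an assumed correlation and runs from slight (ρ = 0.3) to about twice the patients (ρ = 0.7).

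For the functional tests it is conditional. The main-effect shortfall arises only under one reading that the text permits but does not state. Against the group-by-time contrast the loss is moderate at ρ = 0.5 and small at ρ = 0.7. It is larger at ρ = 0.3, where power is 0.63 against 0.91. These figures rest on 0.6 SD, 27 per arm, equal correlations, a constant post-operative effect and complete data, none of which the documents give for these outcomes except the 27.

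The primary flexion-angle t test is not affected. Nor is the sagittal profile, which is already a difference from the native bone.

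**What to change.** - **Functional outcomes.** Model the post-operative visits as responses, with group, visit, group-by-visit and the pre-operative value as covariate. Alternatively, keep the pre-operative visit in the response and constrain its mean to be equal in the two arms. Report the adjusted group difference averaged over the post-operative visits, and at each visit, with 95% CI.
- **Repeated X-ray outcomes.** Use the same baseline-adjusted repeated-measures model for posterior condylar offset, patellar tendon angle, and patellar tilt and displacement at 3 and 12 months.
- **Parameters with no pre-operative value**, such as bone cuts, procedure time and tibial component slope. Keep the t tests or chi-square tests.

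If an analysis plan that is not shown here already says this, the Statistical analysis section need only be brought into line with it. The cost is wording alone: Table 3 already schedules the pre-operative values for the functional tests and X-ray measures named here, and no visit, measurement or patient is added.

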Up till now, the literature has not been conclusive which of the rods should be used, and acknowledges the dilemma of implanting the femoral component either according to the anatomy of the distal femur, or according to the longitudinal axis of the femur in the sagittal plane, thus ignoring sagittal bowing. The standard rod is considered a safe option. However, it is hypothesized that with the flex rod, less bone needs to be removed because the femoral component better fits to the natural anatomy of the distal femur in the sagittal plane. This would lead to more natural femorotibial kinematics through increasing the patellar tendon moment arm, and thus the possibility for larger knee power output without influencing muscle strength. This effect has been found in a modeling study [24] and could potentially lead to better functional outcome in vivo. Indeed, patient-reported functional outcome is higher up till 2 years in patients operated using the flex rod when compared the standard rod [17]. It is expected that due to less oversizing in the TKA procedure using the flex rod activities of daily living (ADL) such as stairclimbing, and rising from a chair can be performed more optimally [6]. Marra et al. have also shown in their modeling study that less oversizing resulted in better patellofemoral kinematics during rising from a chair [24]. It is also expected that with the use of the flex rod, the proper fit of the TKA will result in an overall smaller size chosen by the surgeon, as has been found in a retrospectively analyzed cohort and a modeling study [8, 17].

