## Methods/design

### Aim

The primary aim of this study is to compare the flex rod with the standard rod in terms of post-operative sagittal fit of the distal femur. In addition, sizing and post-operative functional outcome will be evaluated.

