### TKA procedure

The surgical technique is a standardized bone-referenced technique. A tibial bone cut is made based on the standard extramedullary jig from the system aiming at resection of 9 mm bone from the unworn lateral side, or 3 mm below a worn medial compartment. The amount of valgus of the distal cut femur jig is set on the femur angle measured on hip-knee-ankle radiographs of the individual patient. A special custom-made aiming device with an offset of 5 mm (for the flex rod) and 10 mm (for the standard rod) referencing from the intercondylar notch is used to standardize the entry points of the two rods (Fig. 1). Sizing of the femur component is done with posterior referencing. Standard 3° of femoral external rotation is used in these series. Necessary soft tissue releases are done for gap balancing. A standard patella resurfacing is done, and the total implant is placed cemented.

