## Discussion

This randomized controlled trial has been set up to assess how the use of a flex rod affects the fit of the TKA and if this results in better functional outcome. As the sagittal fit of TKA is not a standardized outcome measure, we chose to define the fit with two outcome measures: the first being the flexion angle of the femoral component. It is expected that the flexion angle will be larger in the flex rod group as the femoral component is expected to have a better fit to the distal anatomy of the femur. The second outcome measure is the contour of the distal femur, quantified in the anterior sagittal profile and the posterior sagittal profile at various positions. It is expected that for the flex rod group, due to smaller sizing of the femoral component, the distal anatomy of the femur with TKA will be closer to the pre-operative distal anatomy. We expect that this will be most apparent in the anterior profile where the effect of overstuffing after use of the standard rod is expected to be largest [17]. Also, for this reason, patients in this trial will receive a posterior stabilized TKA, standardizing the posterior placement of the femoral component (in contrast to a cruciate-retaining TKA), and with differences in the anterior part of the distal femur as the only degree of freedom.

Custom-made software is used for calculating the parameters of sagittal fit of the TKA. Due to the unavailability of existing software for measuring the specific parameters for the specific model of TKA, this software was produced in-house. The advantages of this software is that it is tailored made for the study-specific parameters. Disadvantages of this software are that currently we have no data on the reliability and validity of the measurements and that by using imaging of the knee, it is unable to account for articular cartilage thickness [20]. During the TKA procedure, the cartilage of the different cuts will be scored. Using this information, the measurements of the sagittal profile can be corrected for cartilage thickness of 0, 1, and 2 mm, with the values based on the literature [20]. Other parameters that are measured during the TKA procedure are the sagittal thickness (in millimeters) of the cuts, and the area of the cuts. It is expected that due to a better fit of the femoral component to the distal anatomy in the flexible IM rod group, less bone has to be cut, resulting in lower thickness and smaller area of these cuts.

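### Component size and bone-cut area are compared without adjusting for the patient's femur size, which costs precision on the sizing aim although suitable baseline measures are already collected

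*Protocol article*

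**What the plan says.** The Aim section of the protocol article puts fit first and then adds: "In addition, sizing and post-operative functional outcome will be evaluated". The Background gives the sizing question a direction, expecting that "the proper fit of the TKA will result in an overall smaller size chosen by the surgeon". The Discussion predicts that with the flexible rod "less bone has to be cut, resulting in lower thickness and smaller area of these cuts".

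Component size, cut thickness and cut area are listed in Table 2. The Operative information paragraph, under Other study parameters, refers to that table: "See Table 2 for an overview of the parameters recorded during surgery". In the table, cut area is in mm² and cut thickness in mm. The row "Size of components" has its scale entered as n/a.

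For this group of parameters the Statistical analysis section states that "Independent *t* tests (or non-parametric equivalent) and Chi square (in case of frequencies) will be used to analyze the effect of group". It mentions no covariate.

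Two other places matter. The TKA procedure section says "Sizing of the femur component is done with posterior referencing", so size is read from the individual femur. Baseline information includes gender and height, and Table 3 schedules pre-operative 3D imaging and a pre-operative lateral X-ray for every patient.

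**The concern.** A patient with a large femur gets a large component with either rod. The rod can only move the size around that patient-specific value. An unadjusted comparison leaves all the between-patient variation in femur size in the error term, and with 30 patients per arm that can hide a modest shift. Cut area is open to the same problem, since a larger femur plausibly gives larger cut surfaces.

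Smaller sizing is one of the routes by which the Discussion expects the flexible rod to improve fit. A weak test could leave that link unresolved when the data already held could have settled it. The n/a entry for the scale of component size adds a second weakness. It leaves open whether size will be analysed as a number, by ranks or as frequencies, and the last of these leads to a chi-square test that does not use the order of the sizes.

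**Working it through.** **The plan's own figure.** The article gives no power or detectable effect for size or bone cuts. Its only calculation is for the flexion angle: 6° against 11°, SD 5°, α = 0.05, power 0.80, giving 27 per group and, with 10% dropout, 54/(1 − 0.1) = 60. With those inputs (d = 5/5 = 1.0) a two-sided t test needs 17 per group, and 27 per group corresponds to power 0.95. That discrepancy is a separate matter. Only the planned 30 per arm enters the check below. Size and cut area are recorded around the operation, so later dropout does not reduce them.

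**Inputs.** n = 30 per arm; two-sided α = 0.05 (the article does not state sidedness); correlation r between the outcome and a pre-operative femur measure, assumed from 0.3 to 0.9.

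**Formulas.** For a difference of d SD, the power of the unadjusted t test comes from the noncentral t distribution with noncentrality d·√(n/2) and 2n − 2 = 58 degrees of freedom. With one covariate the residual variance is multiplied by 1 − r², so the noncentrality becomes d·√(n/2)/√(1 − r²), with 2n − 3 = 57 degrees of freedom.

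| r (assumed) | 1 − r² | Detectable effect at 80% power (SD) | Power for a 0.5 SD effect | Equivalent sample factor 1/(1 − r²) |
|---|---|---|---|---|
| unadjusted | 1.00 | 0.74 | 48% | 1.0 |
| 0.3 | 0.91 | 0.70 | 51% | 1.1 |
| 0.5 | 0.75 | 0.64 | 59% | 1.3 |
| 0.7 | 0.51 | 0.53 | 76% | 2.0 |
| 0.8 | 0.36 | 0.44 | 89% | 2.8 |
| 0.9 | 0.19 | 0.32 | 99% | 5.3 |

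Hand check from the unrounded 0.736: 0.736 × √0.75 = 0.64 and 0.736 × √0.51 = 0.53.

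**In units of component size.** Component size was simulated with 30 per arm and 3000 runs per setting. It was a femur-driven value (mean 4.5, SD 1.0 to 1.3) plus other variation (SD 0.4 to 1.0), rounded to sizes 1 to 8. All of these are assumptions. They give a size SD of about 1.4 to 1.5, for example √(1.3² + 0.4² + 1/12) = 1.39, and r from 0.69 to 0.93. The rejection rates were:

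| True shift | t test | Mann-Whitney | Unordered chi-square | ANCOVA |
|---|---|---|---|---|
| none | 5–6% | 5–6% | 3–4% | 5% |
| half a size | 26–29% | 24–27% | 7–9% | 45–97% |
| one size | 73–79% | 71–77% | 32–37% | 95–100% |

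The ANCOVA column uses the true femur value as covariate. Sex and height are proxies for it and would be expected to gain less.

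**Scale of chance differences.** With a size SD of 1.4, the standard error of the difference between arms is 1.4 × √(2/30) = 0.36 sizes. Half a size is 0.5/0.36 = 1.4 standard errors and a full size is 2.8.

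**The case against.** The strongest reply is that nothing here is invalid. Patients are randomised, so unadjusted comparisons are unbiased. In the simulation without an effect, the t and rank tests held their error rate at about 5% and chi-square was somewhat below it. A chance imbalance in sex or height is ordinary sampling variation, which the unadjusted standard error already covers. All of that stands.

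A reader might also infer that the plan commits component size to an unsuitable test. The article does not say so. Chi-square is reserved for frequencies, no sentence assigns it to size, and a t or rank test uses the order of the sizes and can address the prediction of a smaller one. The weakness is that the choice is left open.

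Two further inferences lack support. The article does not show that cut thickness depends on femur size; with a standardised bone-referenced technique the dependence may be slight. It gives no expected frequency for recuts or complications either, so it cannot be shown that chi-square would fail there through small counts.

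It can be said that fit already uses each patient as their own reference, because the native profile length is subtracted from the component length. That holds for the sagittal profile. It does nothing for raw component size or cut area.

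Finally, covariates for non-primary outcomes are often left to an analysis plan. Here, however, the article names the tests, and as named they are unadjusted.

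**Conclusion.** The point holds as a matter of precision. Sizing is a named aim with a directional prediction. The tests stated for component size and cut area leave femur size in the error term, although usable baseline measures are collected.

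At 30 per arm, adjustment would lower the detectable effect from 0.74 SD to about 0.64 SD at r = 0.5 and 0.53 SD at r = 0.7. The size of the gain rests on r, which the article does not give. At r = 0.3 it is small (power for a 0.5 SD effect rises from 48% to 51%), and it becomes large only from about 0.7. Dependence on the femur follows from the sizing procedure for component size, is plausible for cut area, and is not shown for cut thickness.

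The documents do not support a conclusion of bias, of a wrong error rate or of an invalid test. Nor should a reader expect chance alone to produce a full-size shift readily: under the assumed SD, that would be 2.8 standard errors.

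**What to change.** In the Statistical analysis section:

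- Name femoral component size as an ordered or numeric outcome, in place of the n/a scale in Table 2. Analyse it by ordinal or linear regression on group, and state that an unordered chi-square test will not be used for it.
- Analyse cut area by ANCOVA on group.
- Adjust both for the same covariate, fixed in advance: either one pre-operative femur dimension, or sex and height.
- Treat the same adjustment for cut thickness as optional.

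If a femur dimension is chosen, it should be measured on the pre-operative image alone. The native profile lengths described under Secondary study parameters are taken on slices placed at 17.1% of the prosthesis width, after alignment carried over from the post-operative image. They can therefore depend on the implanted component and are not clean baseline covariates. A dimension taken without reference to the implant avoids this, for example the posterior condylar offset on the pre-operative lateral X-ray.

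The cost is a change of wording before the data are analysed. Sex and height need no new data. A femur dimension needs at most one further reading of images already scheduled.
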